#### SECONDARY ANALYSIS (STRATIFICATION BY GESTATIONAL AGE)

Besides the analysis that guides the design of the study, both logistic regression and survival analysis will be performed as follows:

- (1) For data collected at  $38^{5/7}$ - $39^{6/7}$  weeks of gestation: Probability of outcome in 7 and 14 days after data collection.
- (2) For data collected at 40 weeks ( $40^{0/7}$ - $40^{6/7}$ ) of gestation: Probability of outcome in 7 and 10 days after data collection.

The same censorship criteria will be applied.

All statistical analysis will be performed using Stata 16.1 software (StataCorp, Texas, USA).

### 4.2. Handling of missing data

As it has been mentioned in the sample size estimation, the required number of participants has been increased in order to compensate potential loss, mainly due to the arising of medical complications that may lead to elective cesarean deliveries or to an induction of labor due to causes different from gestational age. We consider that delivering outside the Hospital is an unlikely event, as the eligibility criteria specify that women plan to deliver within the center.

Missing data in the predictive variables will lead to the exclusion of the participant from the regression models. Hence, a 10% increase in sample size has been estimated to compensate this issue.

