### SAMPLE SIZE

According to our data, approximately 78% of women will start their labor spontaneously before 41 weeks, meaning that 22% will have an induction of labor for medical reasons other than gestational age. Hence, considering 10 events (spontaneous onset of labor) for each of these 15 variables, and doubling this quantity for the elaboration of two different models, 13 participants will be required for each of these variables, hence 390 women are needed. Assuming a 10% rate of women with missing values in at least one predictor, 429 **patients** are needed.

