## 4 STATISTICS AND METHODOLOGY

### 4.1. Statistical analysis plan

#### MAIN ANALYSIS

The main outcome (spontaneous onset of labor vs. induction of labor between 41 and 42 weeks of pregnancy due to gestational age) will define two groups. The distribution of continuous or categorical variables among the units will be compared using Student's T test or Fischer's exact test, respectively. Two-sided significance level was set to 0.05.

A model of prediction of the binary outcome will be elaborated using stepwise backward and forward logistic regression analysis, including all analyzed features (gestational age at data collection will be included as an independent variable). To add or remove variables from the model, p-values of 0.05 or 0.10 will be used, respectively. Goodness-of-fit of the model will be evaluated using Hosmer and Lemeshow test and, if multiple models are achieved, the best one will be selected searching parsimony and following Akaike's Information Criterion. Area under the Receiver-Operating Characteristics curve will be used to assess predictive ability of the model. This value will be also calculated using bootstrapping resampling methods (1000 repetitions) to internally validate the results. As only a subset of the sample will have the measurement of cervical stiffness using Pregnotia device (as this assessment was lately introduced), a secondary analysis (following the same principles of the main analysis) will be performed. A correlation analysis will be carried out comparing cervical consistency index evaluated by ultrasound with cervical stiffness assessed using the aspiration device, as both measurement evaluate the same biophysical characteristic of the cervix.

The probability of spontaneous onset of labor for each day after the analysis will be evaluated using survival regression models. The data will be described using Kaplan-Meier's non-parametrical survival function and the predictive model will be estimated using stepwise backward and forward Cox's regression (proportional hazards model). As mentioned before, data regarding women whose labors have been induced due to maternal or fetal indication (different from gestational age) or with prelabor rupture of membrane without spontaneous onset of labor after 12 hours of expectant management will be censored at the time of admission for these causes.

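### Complete-case exclusion is the only missing-predictor rule for the regression models; the 10% inflation nearly replaces the numbers but not the women, and multiple imputation would keep them

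*Protocol*

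**What the plan says.** Section 4.2 sets the rule: "Missing data in the predictive variables will lead to the exclusion of the participant from the regression models". The next sentence gives the compensation: "Hence, a 10% increase in sample size has been estimated to compensate this issue". The sample size text in section 3.1 states the assumption behind it, "Assuming a 10% rate of women with missing values in at least one predictor", and arrives at 429 women. The figure being inflated is derived there as "13 participants will be required for each of these variables, hence 390 women are needed".

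Section 4.1 deals separately with cervical stiffness: "As only a subset of the sample will have the measurement of cervical stiffness using Pregnotia device", a secondary analysis is planned. Of the 15 predictors listed in section 2.2, about 14 are therefore candidates for the main models. Section 4.1 also adds gestational age at data collection.

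The document is not consistent about what the inflation covers:
- Section 3.1 assigns it to missing predictors.
- The first paragraph of section 4.2 says it is mainly for medical complications that lead to cesarean delivery or induction.
- The possible limitations at the end of section 3.3 give an increase of 20% for exclusions after scan findings.
- Section 3.4 says the sample size has also been adjusted for withdrawal and missing outcomes.

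**The concern.** This is a stated method, not a detail left open. As worded, the rule acts on the participant: one unusable image removes a woman whose outcome and other 13 main-model values are recorded.

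Two things are at stake. The first is efficiency, because women who were examined and followed contribute nothing to the models. The second is the population to which the performance figures apply. The AUC, on which section 4.1 rests the assessment of predictive ability, depends on case mix. Under this rule it is estimated only in women in whom every measurement succeeded, whereas section 1 presents the tool as an aid to counselling women generally. Recruiting more women makes up the count but leaves the same kind of woman out.

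**Working it through.** **Inputs from the protocol.** Section 3.1 gives 10 events for each of 15 variables ("considering 10 events (spontaneous onset of labor) for each of these 15 variables"), a factor of two ("doubling this quantity for the elaboration of two different models"), an event rate of 78% ("approximately 78% of women will start their labor spontaneously before 41 weeks"), and 10% of women with any missing predictor.

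**Reproducing the plan's figure.**
- Women per variable: 10 / 0.78 = 12.8, rounded up to 13.
- Evaluable women: 13 x 15 x 2 = 390.
- Recruited women: 390 x 1.10 = 429. The figure is reproduced exactly.

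**What 429 yields under the plan's own assumption.**
- Complete women: 429 x (1 - 0.10) = 386.1, which is 4 (1%) below 390.
- Expected spontaneous labours, counted as the protocol counts them: 386 x 0.78 = 301, against 10 x 15 x 2 = 300.
- Break-even rate of any missing predictor: 1 - 390/429 = 9.1%.
- Recruitment needed to end with 390 at 10%: 390 / 0.90 = 433.3, so 434, or 5 more than planned.
- Chance of at least 390 complete women out of 429 when each is complete with probability 0.90 (binomial): about 30%.

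These figures use the whole 10% for missing predictors and leave nothing for the other losses that sections 3.4 and 4.2 charge to the inflation. An increase of 20% would give 390 x 1.20 = 468, which is not the recruitment figure.

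**How the loss depends on the missing rate.** The protocol gives no rate per predictor or per procedure, so the rates here are assumptions. With k units missing independently at rate m, the share of women with any gap is 1 - (1 - m)^k.

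| Assumption | Any missing | Complete of 429 |
|---|---|---|
| 14 predictors, 1% each, independent | 13.1% | 373 |
| 14 predictors, 2% each, independent | 24.6% | 323 |
| 4 procedures, 1% each | 3.9% | 412 |
| 4 procedures, 2% each | 7.8% | 396 |

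The last two rows assume that record items are complete and that gaps arise per procedure (digital examination, transvaginal scan, transabdominal scan, vaginal sample). Under independence over 14 predictors, 10% overall corresponds to 1 - 0.90^(1/14) = 0.75% per predictor.

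**What imputation would keep.** At the protocol's 10%, 429 - 386 = 43 women would stay in the models, before losses for any other reason.

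**The case against.** The strongest reply is that the loss is already budgeted. The protocol foresees 10% of women with a gap and raises the sample for that purpose. At that rate it ends 4 women short with the intended 300 events still met, and the shortfall comes from multiplying by 1.10 where dividing by 0.90 was needed. All of this stands.

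A reader might infer that the 390 target is seriously threatened, with only about 323 to 373 women left. The document does not support that. Those figures need independent gaps, yet four predictors come from one transvaginal scan and two from one vaginal sample. Gaps would cluster by procedure, and at a given rate per predictor the loss would be smaller. Nothing in the protocol shows that 10% is too low, but it gives no source for 10% either.

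A reader might also infer that missingness follows the state of the cervix and biases the model. That link is documented only for stiffness, which section 3.1 says is not measured when the cervix is dilated, and stiffness has its own subset analysis. For the main-model predictors the possible limitations mention poor images, with training to reduce them, and do not mention failed samples. Predictors are measured before the outcome and results are blinded, so missingness driven directly by the outcome is unlikely, and complete-case logistic coefficients need not be biased.

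Nor does the rule reach every analysis. It names the regression models, not the single-predictor accuracy analyses in the secondary objectives.

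What survives the reply is that inflation cannot put the excluded women back into the population that the AUC describes, and that no analysis is planned to show whether their exclusion matters.

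**Conclusion.** The point holds as one of efficiency and representativeness. Complete-case exclusion is the only approach specified for the regression models, and it discards women with mostly complete records. At the protocol's own 10% the numerical cost is about 43 women dropped and 386 complete against 390, so the allowance is without margin but nearly adequate on that count. A materially larger loss is possible only at missing rates above 10%, which the document neither gives nor rules out. The size of any shift in the AUC cannot be derived from the protocol.

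The case for imputation assumes that gaps are missing at random given the recorded predictors and the outcome. The 386 assumes that the full 10% is available for missing predictors, which the conflicting statements about the inflation leave open. The change is worth making because it needs no further recruitment or visits.

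**What to change.** Prespecify multiple imputation by chained equations (for example at least 20 sets) as the main approach for the logistic and Cox models:
- Include all main-model predictors, gestational age at assessment and centre in the imputation model. Add the binary outcome for the logistic model, and the event indicator with the cumulative hazard for the Cox model.
- Do not impute stiffness, which is absent by design in part of the sample. State explicitly that it is left out of the main models.
- Select variables on pooled Wald tests and pool the AUC across the imputed sets. Repeat imputation and selection within each bootstrap sample.
- Keep the complete-case analysis as the sensitivity analysis.

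In the sample size text, state that 429 gives about 386 complete women at 10% missing and give a source for the 10%. If complete-case analysis stays as the main approach, use 390 / 0.90 = 434. Reconcile what the 10% in sections 3.1 and 4.2 and the 20% in the possible limitations are each meant to cover.

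The cost is protocol or SAP wording, more programming and a slower bootstrap. AIC and the Hosmer-Lemeshow test would have to be reported per imputed set or on the complete cases, and the plan should say which.

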## **5 REGULATORY ASPECTS AND SAFETY**

### **5.1 Local regulations / Declaration of Helsinki**

This research project will be conducted in accordance with the protocol, the Declaration of Helsinki [3], the principles of Good Clinical Practice, the Human Research Act (HRA) and the Human Research Ordinance (HRO) [1] as well as other locally relevant regulations. The Project Leader acknowledges his responsibilities as both the Project Leader and the Sponsor.

### **5.2 Notification of safety and protective measures (HRO Art. 20)**

The project leader is promptly notified (within 24 hours) if immediate safety and protective measures have to be taken during the conduct of the research project. The Ethics Committee will be notified via BASEC of these measures and of the circumstances necessitating them within 7 days.

### **5.3 Serious events (HRO Art. 21)**

If a serious event occurs, the research project will be interrupted, and the Ethics Committee notified on the circumstances via BASEC within 7 days according to HRO Art. 21. The manufacturer of the Pregnolia Device will be informed about Serious Adverse Events or any related adverse events (Adverse Device Effect).

### **5.4 Radiation**

No radioactive sources will be used during the development of the research project. Ultrasound examination will be performed following ALARA (As Low As Reasonably Acceptable) criteria.

### **5.5 Amendments**

Substantial changes to the project set-up, the protocol and relevant project documents will be submitted to the Ethics Committee for approval according to HRO Art. 18 before implementation. Exceptions are measures that have to be taken immediately in order to protect the participants.

### **5.6 End of project**

Upon project termination, the Ethics Committee is notified within 90 days. Data will remain encoded and anonymized and all forms will be destroyed following current legislation. Ultrasonographic images will be deleted from hard drive devices. Health-related data will be anonymized upon termination of data analysis and safely stored.

### **5.7 Insurance**

As it is a study category A, no insurance is needed.

---

 A serious event is defined as any adverse event where it cannot be excluded, that the event is attributable to the sampling of biological material or the collection of health-related personal data, and which:

- a. requires inpatient treatment not envisaged in the protocol or extends a current hospital stay;
- b. results in permanent or significant incapacity or disability; or
- c. is life-threatening or results in death.

## 6 FURTHER ASPECTS

### 6.1 Overall ethical considerations

Women's opinions in the matter of induction of labor, in the current clinical setting, must be considered. In fact, many women are uncomfortable with the idea of facing an IOL and more than half of them would rather not repeat the experience in subsequent pregnancies. Therefore, any safety concern, especially when the benefit is limited, must be outweighed with maternal perceptions, choices and points of view. Hence, guidelines with universal recommendations of IOL at certain gestational ages might not be followed by women who are against this policy. So, the development of a predictive tool might offer data that will aid in the decision-making process.

The participation in the study will represent for women time effort and the need to subject to extra ultrasonographic explorations. However, these have already demonstrated their lack of deleterious effect on the pregnancy, therefore no harm is expected over maternal or fetal health.

Data will be collected in a form specifically designed for this purpose, adequately codified and anonymized, in order to avoid the possibility of identification and association of sensible data to concrete participants. All the information will be confidentially handled and will remain digitalized in an informatized database, password protected and only accessible by the main researcher. Data will be encoded for any kind of transport and all forms will be destroyed following current legislation. Any incidental finding during analysis will be carefully evaluated and only pondered in the conclusions as *hypothesis-generator*, considering the multiple biases introduced by the assumption of true findings after studies which were not designed for these purposes.

The study will be carried out following the *Good Clinical Practice*, the principles of the *Declaration of Helsinki* and the *Medical Research Involving Human Subjects Act (WHO)*.

Given that the nature of the study is non-experimental (observational) and that the security of the interventions has been widely evaluated during pregnancy, women are not exposed to any risk due to their participation in this research. Likewise, different ethical aspects have been assessed, without finding any conflict open to modifications. All participants will be adequately informed, both orally and in writing, and the main research will remain at their disposal to answer any question that they may find necessary. They will also sign the informed consent form before performing any intervention and they will have the possibility to withdraw from the study at any point, without changes in medical standard of care. They will also have access to the verification of the personal information kept by the researchers and will be notified of the results of the study.

### 6.2 Risk-Benefit Assessment

Apart from the benefit for current scientific knowledge and the potential impact in future management of pregnancies, we do not expect immediate benefits for the participants. However, the study does not represent any risk to women, as the explorations that will be carried out are usually performed in current standard of care. Also, as all data will remain anonymized, there is no risk of personal data diffusion and participant identification if unauthorized data access occurs. Therefore, the risk-benefit balance is clearly leaning to the second.

### 6.3 Rationale for the inclusion of vulnerable participants

The inclusion of pregnant women is mandatory for studying the situations involving the delivery. The risk for the participants is minimal, as the interventions are currently performed during pregnancy and have already demonstrated its safety both for the mother and the fetus. The results of the research will have an impact over the management of pregnant women.

## 7 QUALITY CONTROL AND DATA PROTECTION

### 7.1 Quality measures

Data will be collected by the researchers in specifically designed electronic Case Report Forms, assuring the maximum number of closed questions. All data will be double entered to the database only by the researchers who were trained to handle it, with adequate knowledge in data management and confidentiality. One of the researchers -who was not in charge of data recording- will evaluate data entry by aleatorily selecting a 10% of the forms and verify their correct entrance into the database. Also, inadequate or missing values will be periodically assessed, in order to evaluate data quality. This will be periodically performed at all recruiting centers.

For quality assurance the Ethics Committee may visit the research sites. Direct access to the source data and all project related files and documents must be granted on such occasions.

### 7.2 Data recording and source data

Data will be recorded using electronic Case Repot Forms using Redcap® software. Team researchers will be specifically trained to adequately manage this information using this platform and each center will be responsible of entering the data they produce.

Data will be retrieved from three different sources:

- Biochemical results will be immediately obtained after processing the samples and they will be recorded by the researchers, completely blinding clinicians and participants from results.
- Ultrasonographic images will be recorded in Digital Imaging and Communications in Medicine (DICOM) format and analyzed off-line using specific software.
- Maternal characteristics and perinatal results will be collected from clinical records.

### 7.3 Confidentiality and coding

**Project data** will be handled with uttermost discretion and is only accessible to authorized personnel who require the data to fulfil their duties within the scope of the research project. On the CRFs and other project specific documents, participants are only identified by a unique participant number.

Participant identification lists, and data will be stored in Redcap® databases, which will be password protected and only accessible by authorized researchers. Each center will have its own access to the software, with access only to the information that they have introduced. Only the main researchers will have access to the full set of data.

### 7.4 Retention and destruction of study data and biological material

Biological samples (vaginal swabs) will be destroyed after obtaining the result of the analysis, which is performed immediately after its collection. Data will be encoded for any kind of transport and all forms will be destroyed following current legislation, 10 years after finishing recruitment.

## 8 FUNDING / PUBLICATION / DECLARATION OF INTEREST

The developers of fetal Fibronectin determination kits (Hologic®) will provide them, along with the analyzers at no cost for the researchers. Funding and supplies support will be asked to the developers of Placental alpha macroglobulin 1 determination kits (Qiaogen®).

Regarding the collaboration with the enterprise “Pregnotia AG®”, which will be providing the device for the measurement of cervical stiffness, a collaboration contract has been established. One Pregnotia Control Unit , as well as 240 disposable Pregnotia Probes, will be provided free of charge for the conduct of the research.

Both enterprises have been informed that the study protocol will be published, as well as the conclusions of the research, whatever are the results. The design of the study, the data collection, analysis and publication are an exclusive responsibility of the researchers and no interference from the enterprises is expected. Data will not be shared, and the companies will only know the results once the analysis has finished.

The researchers are workers paid by the institutions involved in the study and will not receive any compensation for participating in the study. Once collaboration contracts are established with any of these two companies, SwissEthics will be immediately informed.

The contract regarding multicentric collaboration is attached to this protocol.

# Appendix 1: Schedule of assessments

| Time
(gestational age)                                                                     | 34-38
weeks | 385/7-396/7
weeks | Delivery | 1 week after
delivery |
|-------------------------------------------------------------------------------------------------------|------------------------|----------------------------------------------------|-----------------|----------------------------------|
| Visit                                                                                          | Information     | Visit                                       |                 |                                  |
| Check eligibility criteria                                                                     | +                      |                                                    |                 |                                  |
| Oral and written Information                                                                   | +                      |                                                    |                 |                                  |
| Written consent                                                                                |                        | +                                                  |                 |                                  |
| Check inclusion/
exclusion criteria                                                        |                        | +                                                  |                 |                                  |
| Medical history                                                                                |                        | +                                                  |                 |                                  |
| Participant Characteristics                                                                    |                        | +                                                  |                 |                                  |
| Ultrasonographic examination                                                                   |                        | +                                                  |                 |                                  |
| Vaginal sampling and testing for fetal
Fibronectin and Placental Alpha
Microglobulin 1 |                        | +                                                  |                 |                                  |
| Collection of perinatal outcomes                                                               |                        |                                                    |                 | +                                |
